### Step 2: lumbar structural rectification

Pulling manipulation on the lumbar vertebrae will be used to regulate the pathological condition of the disorder of the facet joint after finishing the relaxed manipulation [35]. First, the patient is required to face the doctor on the side of the bed in a lateral position. The lower limb in the upper part is on the knee, and the other lower limb is naturally straight. The physician stands on the ventral side of the patient, with elbow or hand against the front of his shoulder and the other elbow against the buttocks. The doctor will coordinate the strength with two hands or elbows, which begins with a small amount of rotation of the waist to relax the waist of the patient. Then, therapists gradually increase the angle of rotation of the patient’s waist with relative force until the maximum extent. It usually ends up with the sound of a “click,” which is without special pursuit during the clinical treatment. The same technique is applied to the contralateral lumbar vertebrae.

### Health care education group

The education intervention will be given to the participants with two sessions per week. The first health education session is a group meeting including all of the participants in the control group using a PowerPoint presentation, which will last 30–60 min. An educational booklet and a video will be given to the patients to do the home-based online e-learning module, containing the same content provided in the PowerPoint presentation. The second session will be conducted as one-to-one communication focused on personal needs to guide patients to implement the key education in their lives. This intervention will be maintained by an experienced physical therapist for 12 weeks. The program will include the following two broad components: (1) introduce key concepts of pain biology and (2) present specification of recovery.

Each patient will be given an introduction about the underlying mechanisms, predisposing factors, and prognosis of low back pain. Pain will be explained as the conscious part of the response, which can be influenced by many factors as a protective output. Interventionists will formulate specification of daily routines for patients, for example: keep the back warm; keep a healthy diet and prevent obesity; maintain beneficial posture and abandon bad habitual posture, keeping a normal physiological curvature of the spine; avoid overwork, intense activity, or lifting heavy weights; maintain proper exercise; and maintain a good mental state and be prepared to endure chronic pain patiently for a long time.

### Outcome measurements

The outcome will be measured by three self-report questionnaires, which can reflect the lumbar dysfunction, pain, and quality of life. Six time points will be used to assess outcomes, including baseline (after enrollment); months 1, 2, and 3 (intervention session); and months 6 and 9 (follow-up sessions).

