**Methods/design:**

This study is a randomized controlled trial with parallel-group design including two groups: a Tuina group and a health care education group. A total of 160 eligible participants will be randomly assigned to the groups in a 1:1 ratio. The interventions of both groups will last for 20 min and be carried out twice each week for a period of 12 weeks. The primary outcome is the Oswestry Disability Index. The secondary outcomes include a visual analogue scale and the 36-item Short Form Health Survey. They will be assessed at baseline, at the end of the intervention every month, and during 6 months and 9 months of follow-up by repeated measures analysis of variance. The significance level is 5%. The safety of Tuina and health care education will be evaluated after each treatment session. This study will focus on the value of Tuina and health care education for low back pain and will highlight any differences in the efficacy of the treatments.

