### Primary outcome measurement

#### Oswestry Disability Index

The primary outcome is the subject’s perceived disability, which is assessed by the modified Oswestry Disability Index (ODI) [36]. The ODI consists of ten items, including pain intensity, personal care, lifting, walking, sitting, standing, sleep, sex life, social life, and traveling. According to the extent of disability, each item is scored from 0 to 5. The total score is reported as a percentage, which is actual score/50 (maximum possible score) × 100%. The ODI results will be assessed using a repeated longitudinal analysis.

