#### Statistical analyses

The intention-to-treat principle will be followed in the primary data analysis with IBM SPSS Statistics for Windows version 21.0 software by statisticians who are blinded to the group allocation. The baseline characteristics will be expressed with descriptive statistics for the two groups, which are reported as the mean ± standard deviation. A Kolmogorov-Smirnov test with Lilliefors correction will be used to analyze all quantitative variables to determine whether they follow a normal distribution. Parametric statistics (Tukey test) or nonparametric statistics (Wilcoxon rank-sum test) will be used for the within- and between-group analyses in accordance with the results of the homogeneity and normality analyses. When initial homogeneity and normality of data distribution are found, repeated measures analysis of variance (ANOVA) and ANOVA with Bonferroni *post hoc* statistics will be used to analyze within and between groups. The Friedman test and Kruskal-Wallis test will be used when initial homogeneity but not normality of data distribution is found. If the initial homogeneity is not found, a linear mixed model will be adjusted for the baseline value. Adverse events in each group will be documented as percentage for safety assessments using the chi-square test or Fisher’s exact test. The statistical significance is defined as *P* < 0.05, and the 95% confidence interval will be reported.

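### Baseline is one of six visits in the repeated measures ANOVA; if its group main effect is read as the treatment effect, the ODI difference is diluted to 5/6.

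*Protocol article*

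**What the plan says.** The Outcome measurements section counts baseline as an outcome visit: "Six time points will be used to assess outcomes, including baseline (after enrollment". The other five are three monthly visits during treatment and two in follow-up, at months 6 and 9. That is one pre-treatment value and five later ones.

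The abstract (Methods/design) names repeated measures ANOVA as the method for the same visits: "They will be assessed at baseline, at the end of the intervention every month". The two follow-up visits stand in the same sentence. For the primary outcome, the Oswestry Disability Index section adds "The ODI results will be assessed using a repeated longitudinal analysis". The VAS and SF-36 sections say the same of those scales.

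The Statistical analyses section has three branches:
- With homogeneity and normality: "repeated measures analysis of variance (ANOVA) and ANOVA with Bonferroni". This serves both the within-group and the between-group comparisons. No baseline covariate is mentioned.
- With homogeneity but not normality: Friedman and Kruskal-Wallis tests.
- Without initial homogeneity: "a linear mixed model will be adjusted for the baseline value".

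A 95% confidence interval is to be reported. The article does not say whether the treatment effect is the group main effect, the group-by-time interaction or a comparison at one visit.

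**The concern.** In a randomised trial the arms differ at baseline only by chance. A between-group main effect averaged over six visits therefore mixes five visits at which treatment can act with one at which it cannot. That average understates the post-treatment difference and is harder to distinguish from zero. The same ANOVA makes no use of baseline as a covariate, which is where the baseline value would gain precision. At stake are the size of the primary ODI difference, the position of its confidence interval, and power in a trial of 80 patients per arm.

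**Working it through.** **Inputs.** From the protocol: six visits, five of them after baseline; 80 per arm; 10% dropout, so 80 × 0.90 = 72 per arm; significance level 0.05, taken as two-sided; power 0.80. The protocol gives no ODI standard deviation, difference or between-visit correlation. Its sample size rests on response rates of 95% and 85%, so there is no ODI figure to reproduce. Assumed here: unit SD, compound symmetry with correlation r, and a constant effect d after baseline.

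**Estimate.** The six-visit group effect is (0 + d1 + d2 + d3 + d6 + d9)/6 = 5/6 × the mean of the five post-baseline differences. This needs no assumption about r or about how the effect varies over time. A mean difference of 0.40 SD is estimated as 0.40 × 5/6 = 0.33 SD.

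**Variance of a patient's mean.**
- Six visits: V6 = (1 + 5r)/6
- Five visits: V5 = (1 + 4r)/5
- Five visits, baseline as covariate: VA = V5 − r²

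The standard error of the arm difference is √(2V/72).

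**CI width.** The ratio of six-visit to five-visit width is √(V6/V5). It is 0.973 at r = 0.3, 0.986 at 0.5 and 0.993 at 0.7. The width hardly changes.

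**CI coverage of the mean post-baseline difference (r = 0.6, d = 0.40).** V6 = 0.6667, so SE = √(2 × 0.6667/72) = 0.136. The shift is 0.40/6 = 0.0667, or 0.490 SE. Coverage = Φ(1.96 − 0.490) − Φ(−1.96 − 0.490) = 92.2%.

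**Power lost by including baseline alone.** Set d so that the unadjusted five-visit mean has 80% power. The ratio of the test statistics is (5/6) × √(V5/V6).

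| r | Ratio | Six-visit group effect |
|---|---|---|
| 0.3 | 0.856 | 67% |
| 0.5 | 0.845 | 66% |
| 0.7 | 0.839 | 65% |

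**Power against the adjusted five-visit model.** Set d so that five visits with baseline as covariate have 80% power: d = 2.8016 × √(2VA/72). At r = 0.6, VA = 0.68 − 0.36 = 0.32 and d = 0.264. Then:
- Five visits without the covariate: 0.264/√(2 × 0.68/72) = 1.92, power about 48%.
- Six visits: 0.264 × (5/6)/0.136 = 1.62, power about 37%.

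The six-visit figure is 51% at r = 0.4 and 29% at r = 0.7. At r = 0.6, about 32 of the 43 points lost come from dropping the covariate and about 12 from including baseline (rounded). At r = 0.7 the covariate accounts for 41 of 51.

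**Group-by-time test.** With a constant effect after baseline, the squared deviations of (0, d, d, d, d, d) from their mean sum to (5/6)d². The noncentrality is (72/2)(5/6)d²/(1 − r), on 5 and 5 × 142 = 710 df. At the d that gives the adjusted model 80% power, this test has 28% at r = 0.4, 38% at 0.6 and 42% at 0.7. At the larger d that gives the unadjusted five-visit mean 80%, it has 30% at r = 0.3, 55% at 0.5 and 90% at 0.7.

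**The case against.** The strongest reply is that the article never names the six-visit group main effect as the treatment contrast. An analyst could use the interaction, or the Bonferroni comparisons visit by visit, and neither is diluted. Naming the contrast may fairly be left to an analysis plan that is not shown. This stands, and it makes the 5/6 result conditional.

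Four stronger readings are tempting, and the documents do not support them.

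- *The confidence interval also shrinks by one sixth.* It does not; it moves toward zero at nearly the same width. If estimate and width both shrank by one sixth, the test statistic and power would not change.
- *The dilution is present in every branch.* Friedman and Kruskal-Wallis tests yield no mean difference averaged over six visits. The mixed model is described only as adjusted for baseline, and nothing says that baseline is also an outcome row. If it were, the dilution would return: simulations at a true 0.40 SD gave 0.33 with baseline on both sides and 0.40 with five outcome visits. That model is an inference from the visit list.
- *Including baseline costs the whole fall from 80% to 37%.* Most of that loss at correlation 0.6 comes from omitting the covariate.
- *Group-by-time is always a weak test.* Against the unadjusted five-visit mean it reaches 90% power at correlation 0.7. It is weak relative to the covariate-adjusted model.

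Keeping baseline as an outcome is also not an error in itself: a longitudinal model that constrains baseline means to be equal across arms does so validly. The article does not describe such a model. Finally, the bias is toward no difference and the coverage loss is modest.

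**Conclusion.** The point holds in conditional form. The article places baseline among the visits analysed by repeated measures ANOVA and gives that branch no baseline covariate. If the group main effect is the treatment effect, the ODI estimate is 5/6 of the mean post-baseline difference; that fraction is exact in expectation under randomisation. The other figures rest on 72 per arm, compound symmetry and assumed correlations: coverage about 92% at 0.40 SD, and power falling from 80% to about 65-67% through including baseline alone. If the analyst avoids dilution by using the 5-df interaction instead, power is still only 28-42% (correlations 0.4-0.7) at an effect for which the covariate-adjusted five-visit model has 80%. On either route the ANOVA branch makes poor use of the baseline value. The point is worth correcting, but it does not invalidate the trial.

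**What to change.** In the Statistical analyses section, state that for the model-based analyses the outcome vector is months 1, 2, 3, 6 and 9, that baseline ODI enters as a covariate only, and that the between-arm difference and its 95% CI come from that model. Say explicitly that the linear mixed model follows the same rule. Apply it to VAS and to each SF-36 domain with its own baseline value. Outcome measurements can still list six collection times, and the abstract's sentence should separate collection from analysis. The cost is a sentence or two, made before the data are analysed; no new patients, visits or data are needed.

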### Primary outcome measurement

#### Oswestry Disability Index

The primary outcome is the subject’s perceived disability, which is assessed by the modified Oswestry Disability Index (ODI) [36]. The ODI consists of ten items, including pain intensity, personal care, lifting, walking, sitting, standing, sleep, sex life, social life, and traveling. According to the extent of disability, each item is scored from 0 to 5. The total score is reported as a percentage, which is actual score/50 (maximum possible score) × 100%. The ODI results will be assessed using a repeated longitudinal analysis.

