#### Safety evaluation

Adverse events refer to the unexpected responses that occur during or after treatment, which can lead to a hospitalization or even threaten life. The trial should be suspended and immediate process is indispensable whenever we encounter adverse events. Also, we should record the details in the case report forms (CRFs). The efficacy and safety of the intervention will be evaluated with 6 months of unsupervised follow-up, during which the subjects should only be received routine lumbar care. At month 6 and 9, participants will be contacted with the phone for their physical condition of low back pain currently. In addition, evaluators can be reformed 13 with the clinical symptoms and AEs whenever the patients meet something important.

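### The primary outcome (ODI) has five post-baseline visits, but neither a deciding visit nor a deciding longitudinal effect is named

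*Protocol article*

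**What the plan says.** The subsection on the Oswestry Disability Index defines the primary outcome without a visit: "The primary outcome is the subject’s perceived disability, which is assessed by the modified Oswestry Disability Index (ODI"). On analysis it adds only: "The ODI results will be assessed using a repeated longitudinal analysis".

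The section on outcome measurements sets the schedule: "Six time points will be used to assess outcomes, including baseline (after enrollment); months 1, 2, and 3 (intervention session); and months 6 and 9". One of the six is baseline, so five visits can carry a treatment comparison: three during the 12-week course and two after it. The abstract singles out none: "They will be assessed at baseline, at the end of the intervention every month, and during 6 months and 9 months of follow-up". The safety section shows that off-treatment results are of interest for efficacy too: "The efficacy and safety of the intervention will be evaluated with 6 months of unsupervised follow-up".

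The statistical analyses section names "repeated measures analysis of variance (ANOVA) and ANOVA with Bonferroni" post hoc tests, both within and between groups, if the data are homogeneous and normal. Otherwise it turns to rank tests or to a linear mixed model adjusted for baseline. Significance is set at 0.05. The section does not say which effect from any of these analyses is the primary one, or which comparisons form the Bonferroni family.

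The sample size section does not settle it either. Its 95% and 85% efficacy rates are tied neither to ODI nor to a visit.

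**The concern.** A repeated-measures ANOVA over this schedule gives several between-group results, and they answer different questions: average benefit (group effect), a different time course (group-by-time effect), benefit at the end of the course (month 3), and benefit that lasts (months 6 and 9). Without a named primary result, the choice can be made after the results are known, and the stated 5% then no longer describes the risk of a false claim.

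There is a second cost. If baseline is one of the repeated levels, the group effect averages in a visit at which randomised groups do not differ in expectation. Someone who takes the group effect as the default primary result would be using a diluted measure of treatment effect.

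**Working it through.** The plan gives no figure for this point beyond the 5% level, so there is none to reproduce.

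**Inputs from the protocol article:** 80 per arm, 10% dropout, two-group design, six time points, level 0.05 (taken as two-sided). Evaluable per arm: 80 × 0.9 = 72.

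**Assumptions:** normal data in SD units; equal correlation ρ between visits, 0.6 unless stated; two effect shapes over baseline and months 1, 2, 3, 6, 9:
- waning: 0, 0.2, 0.35, 0.5, 0.2, 0 SD
- sustained: 0, then 0.35 SD at all five later visits.

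**Step 1. False positives with no true effect.** In simulation at ρ = 0.6, the group effect is significant in 5.0% of trials, the group-by-time effect in 5.0%, and at least one of five Bonferroni visit contrasts (each at 0.05/5 = 0.01) in about 4%. At least one of the three is significant in about 10–11%; at ρ = 0.4 the figure is about 11%. Any one of them, fixed in advance, stays at or below 5%.

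**Step 2. Power of the group effect with baseline as a level.** The effect is the mean over six visits, and the variance of a patient's mean is (1 + 5ρ)/6 = 4/6 = 0.667. SE = √(2/72 × 0.667) = 0.136.
- Waning: 1.25/6 = 0.208; 0.208/0.136 = 1.53; power about 33%.
- Sustained: 1.75/6 = 0.292; 0.292/0.136 = 2.14; power about 57%.

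**Step 3. Group-by-time effect.** Noncentrality is (72/2) × SS/(1 − ρ), where SS is the sum of squared deviations of the six visit effects from their mean.
- Waning: SS = 0.4525 − 6 × 0.2083² = 0.192; 36 × 0.192/0.4 = 17.3; power about 91%.
- Sustained: SS = 0.6125 − 6 × 0.2917² = 0.102; 36 × 0.102/0.4 = 9.2; power about 63%.

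**Step 4. Month 3 adjusted for baseline.** SE = √(2/72 × (1 − 0.36)) = 0.133.
- Waning: 0.5/0.133 = 3.75; power about 96%.
- Sustained: 0.35/0.133 = 2.63; power about 74%.

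**Step 5. Mean of the five post-baseline visits, adjusted for baseline.** Residual variance is (1 + 4 × 0.6)/5 − 0.36 = 0.32, so SE = √(2/72 × 0.32) = 0.094.
- Waning: 0.25/0.094 = 2.65; power about 75%.
- Sustained: 0.35/0.094 = 3.71; power about 96%.

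Simulation agrees with the formulas to within two percentage points:

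| Result taken as primary | Waning | Sustained |
|---|---|---|
| Group effect, baseline as a level | 32% | 56% |
| Group-by-time effect (no direction) | 91% | 61% |
| Month 3, baseline-adjusted | 96% | 73% |
| Post-baseline mean, baseline-adjusted | 74% | 96% |

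**Step 6. How much is dilution?** Dropping baseline without adjusting for it gives SE = √(2/72 × 0.68) = 0.137 and power of about 44% (waning, 0.25/0.137) and 72% (sustained, 0.35/0.137). So part of the loss in the first row comes from averaging in baseline, and the rest from not adjusting for it.

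**The case against.** A repeated longitudinal analysis needs no single primary visit, and details of the model belong in the SAP. The first half is right: one named effect over time would be enough. But which comparison defines the primary result is part of the endpoint, and the article has a section for the primary outcome that leaves it open.

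The plan does mention Bonferroni. That helps, but only in one analysis branch and with no stated family, and it does not cover the choice between group effect, group-by-time effect and visit contrasts. With two groups, a correction among group pairs within a visit covers a single comparison and gives no protection across visits.

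Four stronger readings are tempting, and the documents do not support them.
- *Any significant result would count as a positive trial.* The text is silent on this; it states no such rule. Where Bonferroni is applied over the five visits, a lone month-1 difference would need P < 0.01.
- *The planned ANOVA would miss a waning effect.* Its group effect often would (about 32% power), but the group-by-time test in the same ANOVA is significant in about 91% of trials. Setting 32% against 96% for month 3 also mixes the choice of visit with baseline adjustment: month 3 without adjustment has about 84%.
- *False claims for Tuina double.* The 10–11% includes results favouring education and a test without direction. A group effect or Bonferroni contrast favouring Tuina arises in about 3% of null trials, against a nominal 2.5%.
- *Month 3 is the correct endpoint.* It wins only where the assumed effect peaks there. Nothing in the article says when the effect should peak, and off-treatment efficacy is a stated interest.

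The dilution argument applies to the repeated-measures ANOVA with baseline as a level. The article does not say that baseline is entered so, and its mixed-model branch adjusts for baseline.

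**Conclusion.** The point stands as a gap in the definition of the primary endpoint: five post-baseline ODI visits, on and off treatment, and no visit or longitudinal effect named to decide the trial. Its size is a two-sided false-positive chance of about 10–11% instead of 5% if any of the three kinds of ANOVA result may carry the claim. That is conditional on such freedom being used. If baseline is a repeated level, the group effect is in addition a weak default, with about 32% and 56% power in the two scenarios, against 73–96% for month 3 and 74–96% for the post-baseline mean, both adjusted for baseline.

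The figures rest on 72 per arm, normal data, equal correlation and chosen effect shapes. In the waning scenario, correlations of 0.4 and 0.8 move the group effect to about 43% and 27%, and month 3 to about 90% and over 99%. The calculations support naming one baseline-adjusted contrast; they do not settle which one. That different results would in fact conflict is a possibility, not something the article shows.

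**What to change.** In the Oswestry Disability Index subsection, state one primary between-group contrast, adjusted for baseline ODI and tested once at two-sided 5%. Two candidates are the difference at month 3, the end of the 12-week course, or a pre-specified average over the post-baseline visits. The choice should follow the question the trial is meant to answer: benefit at the end of the course, or benefit over the whole nine months. Declare all other visits, the group-by-time effect and the within-group tests secondary, and make the statistical analyses section agree.

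No new data or visits are needed. The cost is that a difference seen only in another contrast can no longer be called the primary result. Recruitment started in June 2019, so this is a change to a running trial: it must be made before anyone sees outcome data by group, reported to the steering and ethics committees as the quality control section requires, and entered in the registry.
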